## Abstract

**Background:**

Sepsis is a common condition which kills between 36,000 and 64,000 people every year in the UK. Early recognition and management of sepsis has been shown to reduce mortality and improve the health and well-being of people with sepsis. Paramedics frequently come into contact with patients with sepsis and are well placed to provide early diagnosis and treatment.

We aim to determine the feasibility of undertaking a fully powered randomised controlled trial (RCT) to test the clinical and cost-effectiveness of paramedics obtaining blood cultures from and administering IV antibiotics to patients with sepsis, so we can make a decision about whether to proceed to a fully powered randomised controlled trial, which will answer questions regarding safety and effectiveness for patients and benefit to the National Health Service (NHS).

**Methods/design:**

This is an individually randomised, two-arm feasibility study for a randomised controlled trial with a 1:1 ratio. Sixty paramedics will receive training to assist them to recognise sepsis using a screening tool, obtain blood cultures, and provide IV antibiotics. If sepsis is suspected, paramedics will randomly allocate patients to intervention or usual care using their next sequential individually issued scratch card. Patients will be followed up at 90 days using linked anonymised data to capture length of hospital admission and mortality. We will also collect self-reported health-related quality of life (using SF-12) at this time. We will interview ten patients by telephone and hold a focus group with paramedics, to find out what they think about the intervention.

**Discussion:**

At the end of this study, we will make a recommendation about whether a full randomised controlled trial of paramedics obtaining blood cultures and administering IV antibiotics for sepsis is warranted, and if so, we will develop a proposal for research funding in order to take the work forward.

**Trial registration:**

ISRCTN, ISRCTN36856873

**Electronic supplementary material:**

The online version of this article (10.1186/s40814-018-0258-8) contains supplementary material, which is available to authorized users.

## Background

Sepsis is caused by the body’s dysregulated immune response to an infection. It is a time-critical condition which can rapidly lead to multi-organ failure and death [1, 2]. Sepsis has a mortality rate as high as 35%, killing between 36,000 and 64,000 people in the UK every year [3]. More people in the UK die from sepsis than lung cancer or breast and bowel cancer combined [4]. There is evidence to suggest that early diagnosis of sepsis and early administration of intravenous (IV) antibiotics can reduce morbidity and mortality from sepsis [4–6]. The prehospital phase of emergency medical care provides the earliest opportunity for identification of sepsis and delivery of immediate life-saving treatment for patients. It is known that recognition of sepsis in the ambulance can speed up care in the emergency department (ED) and that these patients get the required diagnostics and treatment sooner [7, 8]. Emergency medical services (EMS) personnel may, therefore, play a major role in the identification, pre-alert, and initial management of sepsis. Traditionally, EMS training has focused on assessing and managing ‘barn door’ presentations such as chest pain and ST segment elevation myocardial infarction, stroke and transient ischaemic attack, and acute trauma. To date there has been little focus on the acute assessment and management of sepsis, though the National Early Warning Score (NEWS) system is now used by some EMS providers. Approximately 50% of patients with sepsis in the ED arrive by ambulance [9, 10], with an average prehospital care time of 45 min [11]. This suggests an important window of opportunity for early recognition and care of sepsis before hospital arrival. Despite the importance of this condition and the need for rapid emergency care, the evidence base to support the use of prehospital antibiotics is weak [12, 13], with currently no well-defined prehospital protocol for sepsis in the UK. EMS personnel already play a key role in providing early recognition, initial treatment, and rapid transport for patients with other time-critical conditions; expanding the evidence base on the prehospital management of sepsis is crucial to determining whether earlier identification and management in the prehospital setting could improve health outcomes and speed up care at the ED.

### Feasibility study aim

The aim of this study is to determine the feasibility of undertaking a fully powered randomised controlled trial (RCT) to test the clinical and cost-effectiveness of paramedics obtaining blood cultures from and administering IV antibiotics to patients with sepsis.

### Feasibility study objectives

1. Intervention development:

To work with clinicians, paramedics, pharmacists, and service users to develop a prehospital intervention for sepsis, comprising:A protocol for collection of blood cultures, administration of antibiotics, and handoverTraining for paramedics to deliver the agreed protocol

2. Intervention feasibility:To assess paramedic uptake and satisfaction with the training packageTo assess paramedic compliance with treatment protocolTo determine safety and acceptability of the intervention to patients and paramedics

3. RCT feasibility:To develop and test trial recruitment, randomisation, and data collection processesTo assess sample size requirements and attrition ratesTo determine availability of outcome dataTo clarify primary and secondary outcome measures

4. Full trial planning:To assess our findings against our progression criteria and, if met,Draft a full trial application to the HTA Research Programme

### Progression criteria

We will assess whether or not to proceed to a full multi-site RCT based on the following progression criteria, all of which should be met within reasonable limits (for example, if the progression criterion is within 5% of the target, we will review reasons for this and consider modifications to protocol; if within 10%, we will critically review reasons for this and assess whether major changes to protocol are likely to improve the issue; if more than 10%, we will not progress. The limits for each progression criterion will be stated in our statistical analysis plan; arbitrary limits of 5 and 10% have been suggested here for convenience).

### Intervention feasibility

*Compliance with protocol by paramedics*—no less than 80% of patients recognised as eligible patients by study paramedics are randomised*Acceptability of intervention to patients*—mean patient satisfaction in intervention group is not less than 80% of patient satisfaction in the control group*Safety*—number of patients who experience adverse events has a difference of less than 10% between trial arms*Recognition of sepsis* (*success of training*)(a) At least 50% of patients with sepsis who are attended by study paramedics are recognised as eligible for the study.(b) At least 70% of randomised patients are diagnosed with sepsis in hospital.

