### Participants

#### Patient eligibility

Inclusion criteria:

• Adult patients (18 years or older) with ‘Red Flag’ Sepsis (as defined by the Screening Tool seen in Fig. 1)

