**Fig. 1 Fig1:**
[figure not shown]
Screening tool

• Attended by study paramedics

• Will be conveyed to UHW

Exclusion criteria:

• Pregnancy (known or suspected)

• Known history of allergy to antibiotics

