### Intervention development

A clinical intervention development group comprising paramedics, doctors, nurses, and pharmacists from prehospital care, emergency medicine, critical care, and microbiology met to define the exact treatment protocol and training methods for paramedics to follow early in the study period. They used clinical and local knowledge, research literature, and guidelines from the Joint Royal Colleges Ambulance Liaison Committee (JRCALC) and UHW. Based on advice from Public Health Wales, cefotaxime will be the antibiotic administered to patients in this feasibility study. The Screening Tool and Study Flowchart can be seen in Fig. 1; the screening tool is an adaptation of The UK Sepsis Trust’s Prehospital Sepsis Screening and Action Tool [17]. We decided only to include patients with Red Flag Sepsis in this feasibility study so that we did not broaden the use of antibiotics unnecessarily, in line with antimicrobial stewardship.

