### Data collection

#### Missed recruitments

There are two ways in which patients with sepsis who are attended by study paramedics may not be recruited:The study paramedic does not recognise that the patient has sepsisThe study paramedic recognises that the patient has sepsis but does not randomise them

As part of this feasibility study, we will monitor for missed recruitments so that we can determine whether paramedics are able to accurately recognise patients with sepsis, whether paramedics are compliant with the protocol, and how many patients could not be randomised due to the exclusion criteria. The PRSO will compare recruited patients to all the patients admitted to UHW by study paramedics with sepsis. The PRSO will be able to discuss with individual paramedics any problems or concerns that they may have.

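### Progression criterion 4(a) divides patients recognised as eligible by all patients with sepsis, so a low result cannot separate poor training from case mix

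*Protocol article*

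**What the plan says.** In the protocol article, under Progression criteria, Intervention feasibility, the fourth criterion concerns recognition of sepsis and is glossed as the success of training. Part (a) reads "At least 50% of patients with sepsis who are attended by study paramedics are recognised as eligible for the study".

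Patient eligibility is narrower than sepsis. The section on intervention development states "We decided only to include patients with Red Flag Sepsis in this feasibility study so that we did not broaden the use of antibiotics unnecessarily". Patients must also be adults and "Will be conveyed to UHW". Known or suspected pregnancy and "Known history of allergy to antibiotics" are exclusions.

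Under Missed recruitments, the comparison group is built without a Red Flag filter: "The PRSO will compare recruited patients to all the patients admitted to UHW by study paramedics with sepsis". That section names two routes to non-recruitment (sepsis not noticed; sepsis noticed but patient not randomised) and says that patients barred by an exclusion criterion will be counted. It does not say that they, or sepsis patients without a red flag, leave the denominator of 4(a).

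The opening paragraph of Progression criteria gives illustrative tolerances. A result within 5% of target prompts a review, one within 10% a critical review, and a larger shortfall means no progression. The article calls these limits arbitrary and leaves the final ones to the statistical analysis plan.

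**The concern.** The numerator can contain only patients judged eligible, while the denominator contains every attended patient with sepsis. Someone with sepsis but no red flag, or with an antibiotic allergy, should be left out. When the paramedic does so correctly, the patient still counts against the training measure.

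The criterion therefore mixes two quantities: how well paramedics recognise eligible patients, and how common eligible patients are among those with sepsis. Only the first reflects training. A low figure could mean that training should be changed, or that many sepsis patients fall outside the trial by design. These call for different responses.

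The measure also rises if paramedics call sepsis patients without a red flag eligible, which works against the stated stewardship reason for the restriction. Criterion 4(b) would not detect this, because such patients would still have a hospital diagnosis of sepsis.

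**Working it through.** The article gives no derivation for the 50%, so there is no figure to reproduce. The check is what the criterion measures as written.

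**Inputs**
- Threshold T = 50% (criterion 4(a)).
- Stop line under the illustrative tolerance: 50 − 10 = 40% if the limits are percentage points; 50 × 0.90 = 45% if they are relative. The article does not say which.
- s = share of truly eligible patients whom paramedics recognise as eligible. Unknown.
- q = share of attended sepsis patients who meet all eligibility criteria. Not in the article; assumed range 0.4 to 1.0.

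**Formulae** (assuming no ineligible patient is called eligible)
- Measured rate = s × q
- Sensitivity needed to reach a line L = L / q

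| q | Rate if s = 100% | Rate if s = 80% | s needed for 50% | s needed for 40% | s needed for 45% |
|---|---|---|---|---|---|
| 1.0 | 100% | 80% | 50% | 40% | 45% |
| 0.9 | 90% | 72% | 55.6% | 44.4% | 50% |
| 0.8 | 80% | 64% | 62.5% | 50% | 56.2% |
| 0.7 | 70% | 56% | 71.4% | 57.1% | 64.3% |
| 0.6 | 60% | 48% | 83.3% | 66.7% | 75% |
| 0.5 | 50% | 40% | 100% | 80% | 90% |
| 0.4 | 40% | 32% | unattainable | 100% | unattainable |

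**How q could arise.** Suppose 10% of sepsis patients have an antibiotic allergy and, independently, 20%, 30%, 40% or 50% have no red flag. Then q = 0.9 × 0.8 = 0.72, 0.9 × 0.7 = 0.63, 0.9 × 0.6 = 0.54 or 0.9 × 0.5 = 0.45. The sensitivity needed for 50% is 69%, 79%, 93%, or unattainable. These rates are assumptions, not figures from the article.

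**Stopping.** With perfect recognition (s = 1) the measured rate is q. It falls in the stop zone only if q is below 0.40 (percentage-point limits) or below 0.45 (relative limits). At s = 0.80 the corresponding values are 0.40 / 0.80 = 0.50 and 0.45 / 0.80 = 0.5625.

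**Chance of reaching 50%, ignoring the tolerance.** Take an illustrative 200 sepsis patients and s = 0.80. The binomial probability of at least 100 recognised is 1.00 at q = 0.8, 0.96 at q = 0.7, 0.31 at q = 0.6 and 0.003 at q = 0.5. With only eligible patients in the denominator it is about 1.00 at each of these q.

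**One result, two explanations.** A measured 45% arises from s = 0.90 with q = 0.50 (0.90 × 0.50) and equally from s = 0.50 with q = 0.90 (0.50 × 0.90). An eligible-only denominator would show 90% in the first case and 50% in the second.

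**The case against.** The strongest reply is that little follows from a miss. The criteria need be met only within reasonable limits, and a small shortfall leads to a review of reasons, where case mix could surface. At q = 0.6 and s = 0.80 the measured 48% lies within the 5% band on either reading. This stands, and it limits the consequence. A reader might infer that the criterion could end the programme although paramedics recognise nearly every eligible patient. The documents do not support that as a likely result: it needs a very low q, which they do not give, and the limits are expressly provisional.

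Next, the size is entirely assumed. If q is near 1 the effect is small. The 50% is also the lowest of the minimum-percentage targets and may already allow for ineligible patients. The first part stands. The second is possible, but the article does not say so.

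Third, the missed-recruitment monitoring separates unnoticed sepsis from noticed but unrandomised sepsis and counts exclusions, and its use of UHW admissions deals with the conveyance condition. This partly mitigates. A recognised patient without a red flag could be placed in the second group, but nothing identifies that as a legitimate non-inclusion or carries it into 4(a).

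Finally, the article sometimes uses sepsis as shorthand for the trial population, and the analysis plan, which is not shown, may define the denominator. However, the article defers only the limits of each criterion to that plan; it states the numerator and denominator itself.

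**Conclusion.** The mismatch stands on the article's own wording: as defined, 4(a) is sensitivity multiplied by the eligible share, not a measure of recognition or training alone. Its size cannot be fixed from the article. If 80% of sepsis patients are eligible, the nominal 50% asks for 62.5% sensitivity; if 60% are, it asks for 83%; if fewer than half are, the 50% target itself cannot be reached.

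The main consequence is interpretive: a result below target would not show whether training failed or many patients were rightly left out. Wrongful stopping is secondary and depends on q and on how the tolerance is finally set. The figures assume that no ineligible patient is called eligible; any such error would raise the measured rate. The point merits a change of wording before the criterion is applied, but it does not undermine the study.

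**What to change.** Restate 4(a) so that the denominator is the sepsis patients brought to UHW by study paramedics who, on the PRSO's retrospective review, met the Red Flag criteria and had no exclusion. Require that at least 50% of these were recognised as eligible. The measured rate then equals s whatever q is.

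Red Flag status should not be judged from the attending crew's record alone. Where sepsis was missed because red-flag findings were not sought or written down, the miss would drop out of the denominator and recognition would look better than it was. Use the ambulance record together with existing hospital arrival records, and give a sensitivity figure that counts cases with incomplete ambulance observations as eligible.

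Report the proportion over all sepsis patients as a descriptive second figure.

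The cost is a wording change in the protocol and analysis plan and some extra record review per missed case. The PRSO already compares recruits with all sepsis admissions, but the Quantitative data section describes use of the ambulance record for participants only, so access for missed cases should be confirmed. Some misclassification of Red Flag status in retrospect will remain.

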### RCT feasibility

5.*Acceptability of RCT to paramedics*—at least 60% of eligible paramedics agree to take part in the study6.*Acceptability of RCT to patients*—dissent to take part in the study is 30% or less7.*Retrieval of outcomes*—follow-up data for primary outcome suitable for fully powered trial can be collected for 70% or more of patients8.*Equipoise*—findings indicate that we remain in equipoise about the effectiveness of paramedic obtained blood cultures and prehospital antibiotics for sepsis.9.*Recruitment*—recruitment target met to at least 80%

### Design

Individually randomised (1:1) feasibility trial. The unit of randomisation is the individual patient.

### Setting

The prehospital environment in the urban geographic area serving UHW, Cardiff. Paramedics based at all ambulance stations and fire stations in the Cardiff and Vale of Glamorgan localities of the Welsh Ambulance Services NHS Trust (WAST) will be invited to take part in PhRASe.

### Participants

#### Patient eligibility

Inclusion criteria:

• Adult patients (18 years or older) with ‘Red Flag’ Sepsis (as defined by the Screening Tool seen in Fig. 1)

**Fig. 1 Fig1:**
[figure not shown]
Screening tool

• Attended by study paramedics

• Will be conveyed to UHW

Exclusion criteria:

• Pregnancy (known or suspected)

• Known history of allergy to antibiotics

### Consent

It is acknowledged and accepted that it is not ethically appropriate to consent patients to research within the context of a medical emergency [14]. We have an experience of carrying out randomised trials in emergency care through the SAFER programme and TIER and RAPID feasibility trials [15, 16] and have successfully gained ethical, research, and information governance approvals to inform people of their inclusion in research following their attendance by emergency ambulance. At the time of paramedic attendance, therefore, patients will only be asked to provide consent to have blood cultures collected and receive antibiotics, should they be randomly allocated to the intervention arm. Verbal consent for these procedures will be taken by the paramedics, as would be normally taken for cannulation or venepuncture.

We will provide patients who have been recruited to the study with a Patient Information Sheet, which includes a ‘Participant Dissent Form’. This will be sent at 90 days (30 days for those recruited in the last two months of the study) after the patient’s 999 call. This gives the patient the option to:Decline to receive any further correspondence from the studyHave all of their records withdrawn from the study

Any patients who dissent at this point are taken out of all further involvement, including anonymised follow-up. We have included service users in discussions about this approach which minimises intrusion and possible distress, whilst allowing the opportunity for informed involvement in patient follow-up through qualitative methods. The patient questionnaire sent at 90 days will include a question of whether the patient is willing to take part in an interview about their experiences of 999 care for sepsis. The Paramedic Research Support Officer (PRSO) will check the mortality status of patients before a Patient Information Sheet and questionnaire is sent to minimise distress to bereaved relatives. This means that patients who have deceased are included in our analysis as there is unfortunately no opportunity to give them the option to dissent. The Patient Information Sheet for the study can be seen in Additional file 1.

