#### Sample size

Paramedics will recruit patients over a 6 month period. Based on data regarding throughput of sepsis cases in ED, we estimate a recruitment of approximately 100–150 patients. In this feasibility study, we will not be attempting to detect a clinically significant difference between the intervention and control groups in terms of outcomes, but rather to collect enough data to assess our methods against our progression criteria.

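### Only survivors can be removed by dissent while every death before mailing is kept, so mortality among retained patients is biased upward

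*Protocol article*

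**What the plan says.** All of the rule is in the Consent section of the protocol article. Patients learn of the study by post. On timing the article says "This will be sent at 90 days (30 days for those recruited in the last two months of the study"). Before posting, the Paramedic Research Support Officer (PRSO) "will check the mortality status of patients before a Patient Information Sheet and questionnaire is sent". The form offers two choices: no more letters, or withdrawal of all records. The text then continues: "Any patients who dissent at this point are taken out of all further involvement, including anonymised follow-up". On deaths it says: "This means that patients who have deceased are included in our analysis as there is unfortunately no opportunity to give them the option to dissent".

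Other sections show where the mortality figure goes. Outcomes lists mortality as a candidate primary outcome for the full trial. Analysis plans a chi-squared test with proportions and 95% confidence intervals. It uses the candidate primary outcomes to judge progression criterion 8 (equipoise) and to choose the primary outcome, and it takes estimates from this study for the full trial's power calculation. Criterion 6, under RCT feasibility, requires that "dissent to take part in the study is 30% or less". Blinding states that patients know their allocation.

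**The concern.** Whether a patient stays in the mortality denominator depends on the outcome. A patient who dies before mailing cannot leave, and a patient who survives to mailing can. Each departure removes a survivor and never a death, so the proportion dead among those retained can only rise. The article says openly that the dead are kept, but it does not name the resulting bias or bound it.

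The wording may also enlarge the group removed. One of the two choices is only to stop correspondence, yet the next sentence takes out any dissenter, anonymised follow-up included. Read literally, a wish for no more letters also costs the linked routine outcomes.

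At stake are the event rate carried into the full trial's power calculation, the picture on which equipoise is judged, and the case for or against mortality as primary outcome. Records once withdrawn cannot be restored at analysis, so the rule should be settled before mailing starts.

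**Working it through.** The article gives no expected mortality after dissent, so there is no stated figure to reproduce.

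**Inputs**
- True mortality before mailing, *m*. Background says "Sepsis has a mortality rate as high as 35"%. That is an upper figure for sepsis in general, used here as an illustration; 20% is a further assumption.
- Dissent among survivors who are mailed, *d*. The documents give no forecast. The range 5% to 30% is used, with 30% borrowed from the limit in criterion 6.
- Size: "we estimate a recruitment of approximately 100–150 patients", allocated 1:1, so 50 to 75 per arm.

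**Inflation of the rate.** Deaths stay and a share *d* of survivors leaves:

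observed mortality = *m* / [*m* + (1 − *m*)(1 − *d*)]

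| *m* | *d* | Calculation | Observed | Bias (points) |
|---|---|---|---|---|
| 35% | 5% | 0.35 / (0.35 + 0.6175) | 36.2% | +1.2 |
| 35% | 10% | 0.35 / (0.35 + 0.585) | 37.4% | +2.4 |
| 35% | 20% | 0.35 / (0.35 + 0.52) | 40.2% | +5.2 |
| 35% | 30% | 0.35 / (0.35 + 0.455) | 43.5% | +8.5 |
| 20% | 5% | 0.20 / (0.20 + 0.76) | 20.8% | +0.8 |
| 20% | 30% | 0.20 / (0.20 + 0.56) | 26.3% | +6.3 |

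**Effect on the comparison.** The observed odds of death are the true odds divided by (1 − *d*). Equal *d* cancels in the odds ratio. With true rates of 35% and 30% and 30% dissent in each arm, the observed rates are 43.5% and 38.0%, and the odds ratio is 1.256 before and after.

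Unequal *d* does not cancel. With no true effect, 35% mortality in both arms and dissent of 10% v 30%, the observed rates are 37.4% v 43.5%, a false 6.0 points (odds ratio 0.90/0.70 = 1.29). In 20,000 simulated trials (two-sided 0.05 assumed) this split gave p < 0.05 in 8.9% of trials at 100 patients and 11.2% at 150. With no dissent the figures were 4.6% and 5.1%.

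**Effect on planning.** For 80% power to separate 35% from 30%, 1377 per arm are needed. Entering the inflated 43.5% and 38.0% gives 1250, which is 127/1377 = 9% fewer.

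**Check of the remedy.** Take 75 in an arm, 35% mortality and 30% survivor dissent. There are 26.25 expected deaths and 48.75 survivors, of whom 14.625 dissent and 34.125 stay. Retained mortality is 26.25/60.375 = 43.5%. Counting the 14.625 as alive gives 26.25/75 = 35%, the true rate. This is legitimate up to the mailing date because each was checked alive before the form was posted.

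**The case against.** The strongest reply is that little hangs on this in a feasibility study. Sample size says that no clinically significant difference is sought, Analysis is mainly descriptive and exploratory, and criterion 8 is a judgement with no stated threshold. At 50 to 75 per arm, the 95% confidence interval for the arm difference has a half-width of roughly 17 to 21 points. Even the 6.0-point artefact above is well inside that, and the 9% shift in planned size is small beside the imprecision of rates from so few patients. This stands, and it limits the severity. It does not remove the bias, which has a known direction and is cheap to avoid.

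The inputs are also ceilings. Criterion 4(b) accepts that up to 30% of randomised patients may not have sepsis diagnosed in hospital, so mortality may be below 35%, and 30% dissent is a limit, not a forecast. This stands too.

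Three stronger readings are tempting and not supported:
- A reader might infer that the plan will produce a false arm difference. That needs dissent to differ by arm. Unblinded patients make it possible, but nothing in the article links allocation to dissent.
- A reader might take it as settled that patients who only decline letters lose their routine outcomes. The sentence may be meant for record-withdrawers alone, since otherwise the two choices would be redundant. The operative form is in a supplementary file that is not shown. What can be said is that the two sentences need reconciling. Bias from record-withdrawers remains either way.
- A reader might infer that criterion 6 counts the dead as non-dissenters. The article gives it no denominator, and its remark that the dead cannot dissent fits a denominator of those asked. Stating that denominator is a clarification only.

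The three-monthly safety reports of deaths from routine records do not answer the point. The deaths are not what goes missing; the survivors are.

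**Conclusion.** The concern holds in a limited form. As the Consent section is written, mortality among retained patients is biased upward whenever any survivor dissents. Over the range examined, the bias runs from about 1 point (5% dissent) to 8.5 points (35% mortality, 30% dissent). These are illustrations across assumed values of mortality and dissent, not predictions, and low dissent makes the bias small. Equal dissent leaves the odds ratio intact; any false arm difference is conditional on unequal dissent, which is not shown. The damage is to the mortality estimates behind the equipoise judgement, the outcome choice and the full-trial power calculation, not to a confirmatory test.

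**What to change.** (a) Reconcile the two choices on the form with the sentence that removes any dissenter. Declining correspondence should stop letters only, with anonymised follow-up through the SAIL databank continuing, subject to the approvals. Only a request to withdraw records should remove data.

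(b) Record the number of record-withdrawers per arm and by mailing schedule (90 or 30 days). Report 30-day mortality over all randomised patients with record-withdrawers counted as alive, since each was checked alive at 30 days or later. For 90-day mortality, do the same for those mailed at 90 days. For withdrawers mailed at 30 days, give a best case (all alive at 90 days) and a worst case (all dead by then). Mortality simply to the mailing date should not be used, because it would mix the two horizons. Show these figures beside the complete-record figure.

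(c) As a clarification, state that criterion 6 is taken over patients alive and sent the form.

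The cost is one clarified sentence in the protocol and patient material, a possible ethics notification (including for the use of a bare count of withdrawers by arm), and an extra table row. No new data collection is needed beyond counting the dissent forms by type, arm and mailing schedule.
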